## Methods for Assigning Patients to Treatment

All patients signing the ICF and who enter the formal screening processwill be assigned a unique screening number.

Following successful completion of the screening/baseline evaluations and confirmation that the patient is eligible for participation, the patient will be randomised to treatment or not. This will be performed by the Investigator assigning a randomization number to the patient

## Concomitant Medication

Any medication (prescription as well as over the counter (OTC) drugs) or therapeutic intervention deemed necessary for the patient, and which, in the opinion of the Investigator, do not interfere with the safety and efficacy evaluations, may be continued unless they are included in the list of *‘medications and therapeutic regimens excluded from the study’* outlined below.

Any new medications or changes to the dose or regimen of pre-existing medications will be updated on a routine basis during the study.

Investigational new drugs (i.e. drugs that are not marketed in the local market) should not be co-administered with the study medications during the entire period of the study.

## Study Medication Accountability

Compliance will be monitored with counting of capsules and collection of blister packs.

# RESPONSE VARIABLES AND ENDPOINTS

## Assessment of Efficacy

### Primary Efficacy end-point

The primary end-point is reduction of albumin excretion

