### Efficacy evaluation methods

#### Proteinuria

Measured as albumin/creatinine ratio at baseline and after 12 months.

**Note:** Proteinuria (albumin/creatinine ratio) will be measured automatically for the Baseline (Visit 1, Day 0) and Final Safety Follow-up (Visit 4, Week 48).

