# STATISTICAL METHODOLOGY AND DATA MANAGEMENT

## Study Design

This clinical trial employs a Randomized, open control design. Randomisation is used to minimise assignment bias and to increase the likelihood that known and unknown patient attributes. Estimation of Sample Size:

Assuming a type 1 error of 5% and at type II error of 20 %, with a clinically relevant difference in 5.2 mg/mmol from a baseline value of 15.0 + 10 mg/mmol the estimated number of patients in each arm should be 30, assuming a correlation between start and end value of 0.5. In case of early drop-outs additional patients can be included to ensure that a total number of 70 patients will be randomized.

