## Statistical Analysis Plan

The main hypothesis:

In renal transplant recipients’ treatment with paricalcitol is superior to placebo, and results in reduced albuminuria at 12 months treatment.

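### The primary endpoint is worded and sized as a change in albumin excretion and no baseline-adjusted comparison is specified; naming ANCOVA would gain about 12 points of power on the plan's own inputs

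*Protocol*

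**What the plan says.** Under Primary Efficacy end-point, the protocol says: "The primary end-point is reduction of albumin excretion". The section headed Statistical Analysis Plan contains one hypothesis, that treatment "results in reduced albuminuria at 12 months treatment". The endpoint sentence suggests a fall from baseline, and the hypothesis a lower value at 12 months. Neither names a test, a model or a covariate.

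The Proteinuria section describes the outcome as "Measured as albumin/creatinine ratio at baseline and after 12 months", so both values are planned for every patient. Secondary Efficacy Variables uses the same style of wording: reductions in PTH and pulse wave velocity, an increase in bone mineral density, and changes in biomarkers.

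The sample-size text, in Study Design under Statistical Methodology, is the only quantitative account of the primary comparison. It sets a 5% type I error and 80% power, targets a difference of 5.2 mg/mmol against a baseline mean of 15.0 with a spread of 10, and concludes that "the estimated number of patients in each arm should be 30, assuming a correlation between start and end value of 0.5". Up to 70 patients in total may be randomised. No stratification is described in the Randomisation sections or under Methods for Assigning Patients to Treatment.

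**The concern.** When an outcome is measured before and after treatment, two arms can be compared in three common ways: on the 12-month value, on the change from baseline, or on the 12-month value adjusted for baseline. The third is the most precise at the correlations examined here. At a correlation of 0.5 with equal SDs, the first two have the same precision, so subtracting baseline gains nothing.

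The wording and the sizing both point towards a change score. An analyst who followed them literally would leave unused about a quarter of the variance that baseline ACR can explain. The two wordings also leave two unadjusted estimates open, and these respond to a chance baseline difference in opposite directions. In an open trial it is better to fix the comparison before outcome data are seen.

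**Working it through.** **Inputs**

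- From the sample-size text: difference 5.2 mg/mmol, baseline mean 15.0 and SD 10, correlation 0.5, type I error 5%, power 80%, 30 per arm, and up to 70 in total (35 per arm).
- Assumptions: the plus sign before 10 means plus/minus; the SD is also 10 at month 12; the test is two-sided; ACR is untransformed. The protocol states none of these.

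**1. SD of each comparison**

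- 12-month value alone: 10.0
- Change: 10 × √(2 × (1 − 0.5)) = 10.0
- Baseline-adjusted residual: 10 × √(1 − 0.5²) = 8.66, which is 0.75 times the variance

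**2. The plan's figure of 30 per arm**

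With normal quantiles 1.960 + 0.842 = 2.802:

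- Two arms, SD 10: 2 × (10 × 2.802 / 5.2)² = 58.1, so 59 per arm.
- Two arms, SD 8.66: 43.5, so 44 per arm.
- One-sample paired formula, SD 10: (10 × 2.802 / 5.2)² = 29.03, so 30.
- One-sample paired formula, SD 8.66: 21.8, so 22.

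One-sided two-arm versions give 46 and 35. Only the paired formula with SD 10 yields 30. At correlation 0.5 that SD belongs equally to the change and to the 12-month value. However, a calculation on the 12-month value alone has no use for a correlation, and the plan quotes one. The change score is therefore the natural reading.

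**3. Power by analysis** (noncentral t, two-sided 5%)

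The noncentrality is 5.2 / (SD × √(2/n)). At 30 per arm this is 5.2 / 2.582 = 2.014 unadjusted and 5.2 / 2.236 = 2.326 adjusted.

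| Patients per arm | Change or 12-month value | Baseline-adjusted | Gain |
| --- | --- | --- | --- |
| 30 | 50.8% | 62.8% | 12.0 points |
| 35 | 57.3% | 69.7% | 12.4 points |

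The normal approximation gives 52.2% against 64.3% and 58.5% against 70.9%, which is the same gain.

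**4. If the correlation is not 0.5** (30 per arm, noncentral t)

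| Correlation | Change | 12-month value | Baseline-adjusted | Gain over change |
| --- | --- | --- | --- | --- |
| 0.3 | 38.8% | 50.8% | 54.6% | 15.8 points |
| 0.5 | 50.8% | 50.8% | 62.8% | 12.0 points |
| 0.7 | 72.5% | 50.8% | 79.2% | 6.7 points |

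Adjustment gives the highest power in every row.

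**5. Chance baseline imbalance**

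The standard error of the baseline difference at 30 per arm is 10 × √(2/30) = 2.58 mg/mmol. An imbalance of that size is expected to move the change-score estimate by (0.5 − 1) × 2.58 = −1.29 and the 12-month estimate by 0.5 × 2.58 = +1.29. Each shift is about a quarter of 5.2. Adjustment removes it.

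**The case against.** The strongest reply is that the protocol never calls the comparison unadjusted. A reader might infer from the word reduction that a raw change score has been fixed, but the text does not support that. ANCOVA on the change and ANCOVA on the 12-month value, each with baseline as covariate, give the same treatment estimate, and either fits both wordings. The model and its covariates are also often left to a separate statistical analysis plan, which may exist and was not available here. A start-to-end correlation can be an input to ANCOVA sizing as well. The figure of 30 matches no two-arm analysis, so it is first of all evidence of a sizing error.

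All of this stands as a limit on the claim: the power loss is conditional on an unadjusted analysis being run. It does not remove the point. The endpoint wording, the secondary wording and the only arithmetic in the document all lean towards change, and the section headed Statistical Analysis Plan offers nothing but a lower 12-month value.

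A reader might also infer that an unadjusted change score would be biased by regression to the mean. The documents do not support that either. Patients are not selected on albuminuria and are randomised 1:1, so the unadjusted estimate is unbiased over randomisations. The imbalance in step 5 is a matter of precision already counted in the power figures, not a further loss.

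**Conclusion.** The point holds as a free improvement that should be made, not as a stated error of analysis. The protocol words and sizes its primary comparison as a change and specifies no baseline adjustment, without excluding it. If the analysis follows that wording unadjusted, it gives up about 12 points of power at the planned size.

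The figure of 12 rests on the plan's difference and correlation, an SD of 10 at both times, the untransformed scale and a two-sided test. It would be different on the log scale, for which the protocol gives no inputs.

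Nor should adjustment be read as a repair of the sample size. Even adjusted, power is about 63% to 70% against the planned 80%. By noncentral t, 80% needs 60 per arm for a change score and 45 with adjustment. That shortfall is a separate matter.

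**What to change.** Under Primary Efficacy end-point and Statistical Analysis Plan, state that the primary analysis compares 12-month ACR between arms by ANCOVA, with treatment as factor and baseline ACR as covariate. Both values should be on the same scale, and both logged if ACR is analysed as log. Use the same model for secondary variables that have a baseline value: PTH, pulse wave velocity, bone mineral density and estimated GFR.

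The cost is one or two sentences and one degree of freedom. No extra patients, visits or measurements are needed, since ACR is already collected at both times. The sample-size paragraph needs its own correction.

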### Secondary Efficacy Variables

Secondary efficacy variables will include:

- Proteinuria, measured with albumin/creatinine ratio.
- Fibrosis, evaluated with Interstitial fibrosis/Tubular Atrophy (IF/TA), and expression of fibrosis markers in a kidney biopsy after 12 months
- Reduction in PTH
- Reduction in pulse wave velocity
- Increase in bone mineral density
- Renal function measured assessed by estimated GFR
- Change in circulating inflammatory biomarkers
- Change in biomarkers of bone turnover.

## Assessment of Safety

### Study-specific Safety Variables

If an unexpected, clinically significant change from baseline occurs in a laboratory value or other measurement, the Investigator should repeat the test if appropriate, to verify the result. The Investigator must comment on all clinically significant changes in laboratory values. All clinically significant adverse events must be followed-up and this follow-up documented until the events return to normal or become stabilised.

## Adverse Events and Serious Adverse Events

### Definitions of Adverse Events

#### Seriousness

Adverse Events (AE):

Any undesirable experience occurring to a patient during a clinical study, whether or not considered related to the investigational study medication(s).

All Adverse Events must be recorded in the case report form, defining relationship to study medication and severity. Adverse Events should also be recorded by the Investigator in the patient file/notes.

Serious Adverse Events (SAE):

A serious adverse event (experience) or reaction is any untoward medical occurrence that at any dose results in death, is life-threatening, requires in-patient hospitalisation or prolongation of existing hospitalisation, results in persistent or significant disability/incapacity, or is a congenital anomaly/birth defect, is a medically important event or reaction.

**Note:** The term "life-threatening" in the definition of "serious" refers to an event in which the patient was at risk of death at the time of the event; it does not refer to an event which hypothetically might have caused death if it were more severe.

Medical and scientific judgement should be exercised in deciding whether expedited reporting is appropriate in other situations, such as important medical events that may not be immediately life-threatening or result in death or hospitalisation but may jeopardise the patient or may require intervention to prevent one of the other outcomes listed in the definition above. These should also usually be considered serious.

Unexpected Adverse Event:

An experience not previously reported in the Summary of Products Characteristics (SPC).

#### Severity

Mild:

The adverse event is transient and easily tolerated.

Moderate:

The adverse event causes the patient discomfort and interrupts the patient's usual activities.

Severe:

The adverse event causes considerable interference with the patient's usual activities, and may be incapacitating or life-threatening.

#### Relationship to study medication

Unrelated:

This category is applicable to those adverse events which, after careful medical consideration at the time of evaluation, are judged to be clearly and incontrovertibly due to extraneous causes (disease, environment, etc.) and do not meet the criteria for study medication relationship listed under remote, possible or probable.

Unlikely:

In general, this category is applicable to those adverse events that, after careful medical consideration at the time they are evaluated, are judged to be remotely related to the test study medication. An adverse event may be considered remote if, or when, for example:

1. It does not follow a reasonable temporal sequence from administration
2. It could readily have been produced by the patient's clinical state, environmental or toxic factors, or other modes of therapy administered to the patient
3. It does not follow a known response pattern to the suspected study medication
4. It does not reappear or worsen when the study medication is re-administered

Possible:*(must have first two criteria)*

This category is applicable to those adverse events which, after careful medical consideration at the time they are evaluated, the connection with the test study medication administration appears unlikely but cannot be ruled out with certainty. An adverse event may be considered possible if, or when:

1. It follows a reasonable temporal sequence from administration
2. It could readily have been produced by the patient's clinical state, environmental or toxic factors, or other modes of therapy administered to the patient
3. It follows a known response pattern to the suspected study medication
4. It does not reappear or worsen when the study medication is re-administered

Probable: *(must have first three criteria)*

This category is applicable to those adverse events, which, after careful medical consideration at the time they are evaluated, the connection with the test study medication administration appears to, with a high degree of certainty, be related to the test study medication. An adverse event may be considered probable if:

1. It follows a reasonable temporal sequence from administration
2. It could not be reasonably explained by the known characteristics of the patient's clinical state, environmental or toxic factors, or other modes of therapy administered to the patient
3. It disappears or decreases on cessation or reduction in dose. There are important exceptions when an adverse event does not disappear upon discontinuation of the study medication, yet study medication-relatedness exists; e.g. bone marrow depression, fixed study medication eruptions, and tardive dyskinesias
4. It follows a known response pattern to the suspected study medication
5. It reappears upon rechallenge

Not assessable:

When it is not possible to assign the event to any of the criteria above categories.

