## Serious Adverse Reactions and Unexpected Adverse Reactions

### Definitions

Adverse Reaction:

All noxious and unintended responses to a medicinal product related to any dose should be considered adverse drug reactions.

The phrase "responses to a medicinal product" means that a causal relationship between a medicinal product and an adverse event is at least a reasonable possibility, i.e., the relationship cannot be ruled out.

For marketed medicinal products, an adverse reaction is a response to a drug which is noxious and unintended and which occurs at doses normally used in man for prophylaxis, diagnosis, or therapy of disease or for modification of physiological function.

Unexpected Adverse Reaction:

An adverse reaction, the nature or severity of which is not consistent with the applicable product information (e.g. product information sheet such as the Summary of Products Characteristics (SPC)).

Suspected Unexpected Serious Adverse Reaction (SUSAR):

Any serious adverse reaction that might be related to the study medication and are unexpected according to the definition above.

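### An unexplained, well-timed event during unchanged paricalcitol dosing fits neither Possible nor Probable and is left as Not assessable, although it meets the protocol's own definition of an adverse reaction

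*Protocol*

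**What the plan says.** The section Relationship to study medication sets five causal grades, Unrelated to Probable being four of them and Not assessable the fifth.

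- **Possible** carries the note "must have first two criteria". Criterion 1 is "It follows a reasonable temporal sequence from administration". Criterion 2 is "It could readily have been produced by the patient's clinical state, environmental or toxic factors, or other modes of therapy administered to the patient".
- **Probable** carries the note "must have first three criteria". These are reasonable timing, no reasonable alternative explanation, and "It disappears or decreases on cessation or reduction in dose". Criterion 3 has an exception for events that persist after the drug has been discontinued, with examples.
- **Unrelated** needs a clear extraneous cause. **Unlikely** is for events judged only remotely related, and its criteria are examples rather than requirements.
- **Not assessable** is the residual: "When it is not possible to assign the event to any of the criteria above categories".

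The Definitions under Serious Adverse Reactions and Unexpected Adverse Reactions use a different test. An event is a reaction if "a causal relationship between a medicinal product and an adverse event is at least a reasonable possibility, i.e., the relationship cannot be ruled out". A SUSAR is then a serious, unexpected reaction that might be related. No section says which of the five grades count as related for these definitions.

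**The concern.** The lack of any other explanation normally strengthens the suspicion that a drug caused an event. Here it disqualifies the event from Possible, and Probable then asks for a result that does not exist while dosing continues. The investigator has a suspected reaction and no causal grade for it.

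The situation can arise in ordinary conduct. Study drug is prescribed for the whole study, and the only dose reduction that the protocol spells out is for raised serum calcium (Study drug administration; Paricalcitol Titration). At the first SAE call, due within 24 hours of awareness, the investigator must already give a preliminary view on causality (Reporting of adverse events). The effect of stopping will often be unknown by then.

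At stake is consistent handling of relatedness. The SUSAR section sets limits of seven and fifteen days for reporting to authorities. Whether an event graded Not assessable starts those clocks is left to each reader of the protocol.

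**Working it through.** There is no figure in the protocol to reproduce. The check applies the compulsory criteria to each type of event.

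**Step 1: the case in question.** Timing is reasonable, there is no other explanation, and paricalcitol is continued unchanged or the result of stopping is not yet known.

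- Possible: criterion 1 is met. Criterion 2 ("It could readily have been produced by the patient's clinical state", or another listed cause) is not. Fails.
- Probable: criteria 1 and 2 are met. Criterion 3 is not, because nothing has been observed after stopping or reducing. The exception speaks of events that persist after discontinuation, so it does not reach continued dosing. Fails.
- Unrelated: needs a clear extraneous cause. Fails.
- Unlikely: needs a judgement of remote relation, which does not suit a well-timed event with no other cause.
- Not assessable: all that remains.

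**Step 2: enumeration.** Given reasonable timing, take three states of alternative explanation and four states of dechallenge (what happens on stopping or reducing). Each cell holds 2 × 3 = 6 combinations: known response pattern (yes, no) by rechallenge (positive, negative, not done). The entries count combinations that meet neither Possible nor Probable, with the exception read as satisfying criterion 3.

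| Alternative explanation | Dechallenge positive | Negative, within exception | Negative, outside exception | Not done or not known |
|---|---|---|---|---|
| Readily available | 0 of 6 | 0 of 6 | 0 of 6 | 0 of 6 |
| Reasonable but not ready | 6 of 6 | 6 of 6 | 6 of 6 | 6 of 6 |
| None | 0 of 6 | 0 of 6 | 6 of 6 | 6 of 6 |

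The bottom right cell is the case in Step 1. If the drug was never stopped, no rechallenge can have taken place, so only two of its six combinations are realistic there (response pattern known or unknown). Both are unassigned. With a known pattern, none of the examples under Unlikely is met. With an unknown pattern, one is.

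The middle row has the same origin on a strict reading. Possible asks for a ready alternative and Probable for no reasonable one, and these are not complements, so 4 × 6 = 24 of 24 combinations fit neither.

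**Step 3: comparison with the reaction definition.** The case in Step 1 has reasonable timing and no competing cause, so a relationship cannot be excluded and the Definitions make it an adverse reaction. The protocol's general description of Possible also speaks of a connection that cannot be excluded with certainty. The compulsory criterion 2 thus works against the description of its own grade.

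**Step 4: effect of the change.** If reasonable timing alone is compulsory for Possible, all 6 of 6 combinations in the disputed cell can be assigned, against 0 of 6 now. The middle row is closed by the same step.

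**The case against.** The scale is a guide to medical judgement, and much of what a reader might infer from the gap goes further than the protocol does.

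- **That reportable reactions are lost.** The protocol does not support this. SUSAR status rests on whether a serious unexpected reaction might be related, not on a grade of Possible or Probable. Every potential SAE is to be notified within 24 hours whatever its cause, and an independent committee reviews safety data. Not assessable is not said to mean not related.
- **That sudden fatal events drop out.** The exception to criterion 3 gives its conditions only as examples and can be read to cover irreversible or fatal events. Its application to a death on treatment is unclear, but it cannot be said to exclude one.
- **That a large share of events is affected.** The table counts combinations, not events. These patients are weeks past transplantation and on three immunosuppressants, so a ready alternative cause will often exist. Raised calcium leads to a dose reduction, and unacceptable adverse events are a listed reason for stopping the drug. Both can supply the missing observation.
- **That an event with a weaker causal case is ranked higher.** Not assessable lies off the scale, so there is no strict ranking.

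These points limit the consequence. They do not supply a causal grade for the unexplained event during unchanged dosing. Using Unlikely for it would fit the reaction definition even less well. A statistical analysis plan could group grades for tables but could not restore a grade that the site was unable to give.

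**Conclusion.** The concern holds as a minor defect of drafting. Read as written, the compulsory criteria leave a well-timed event with no other explanation ungraded while paricalcitol continues unchanged or the result of stopping is awaited. The same event satisfies the protocol's definition of an adverse reaction, and the two sections are not connected by any statement of which grades count as related.

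The conclusion assumes that the notes on compulsory criteria are applied literally and that the exception under Probable is limited, as worded, to events persisting after discontinuation. How many events would be affected cannot be derived from the protocol. Under-reporting is possible if a reader treats Not assessable as not related, but the protocol does not prescribe that. The primary endpoint is not touched.

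**What to change.** In Relationship to study medication:

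1. For Possible, make only criterion 1 (reasonable timing) compulsory and keep criterion 2 as a descriptive feature. Amend the description of the grade, which now calls the connection improbable, so that it also fits events with no other explanation.
2. For Probable, require criterion 3 only where dechallenge was done and can be assessed. Some unexplained events will then be eligible for both grades, and the investigator's judgement under the two descriptions decides between them.
3. Add one line linking the scale to the reaction and SUSAR sections: Possible, Probable and Not assessable count as related for those purposes. State how Unlikely is treated, since the same question arises there.

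The cost is a few words in the protocol and matching wording wherever the grades are set out for sites, such as the SAE form. A few more events will be classed as related and possibly reported. No dose or treatment rule is affected.
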